### Study intervention

Both the DPS therapy and SCTT were implemented concurrently to reduce variability caused by seasonal changes in symptom severity. During the four-week intervention phase, participants in both groups received manual therapy according to their assigned treatment. Each group underwent five therapy sessions per week, each lasting 40 min, for a total of four weeks. Participants remained in inpatient rehabilitation during this period, and weekly consultations were held to monitor adherence. The four-week treatment window reflects standard practice in China, where medical insurance typically limits inpatient rehabilitation to this duration.

Participants were instructed not to take nonsteroidal anti-inflammatory drugs (NSAIDs), including celecoxib, or acetaminophen during the trial. Medications such as celecoxib may pose risks for post-stroke shoulder pain patients with a history of cardiac stent placement, as they can impair platelet function and increase cardiovascular risk (7, 16). In cases of severe pain, acupuncture was used as a temporary alternative, integrated into the basic rehabilitation regimen. Routine rehabilitation therapy continued throughout the study to ensure uniformity in care delivery.

### DPS intervention

DPS therapy is composed of two core elements: assessment and treatment. The process begins with a posture assessment, which forms the basis of the intervention. Visual observation is first used to evaluate whether the trunk and limbs are in a neutral alignment. This is followed by palpation and movement testing to identify any joints or muscle groups that deviate from their neutral positions. The assessment includes a full postural evaluation of the trunk and the shoulder complex in a neutral stance. A distal-to-proximal approach is applied, examining the lumbar spine, thoracic spine, and both cervical and shoulder regions across the coronal, sagittal, and transverse planes. The shoulder complex is then assessed on both sides, focusing on the sternoclavicular joint, acromioclavicular joint, scapulothoracic articulation, and glenohumeral joint to detect any asymmetry or structural abnormality.

Using a patient with right-sided post-stroke shoulder pain as an example, common postural deviations include lumbar spine lateral flexion toward the hemiplegic side, thoracic kyphosis, and scapular depression. The 4R technique is applied to correct these issues. The procedure involves the following steps: (1) With the patient in a seated position, the therapist stabilizes the left lumbar transverse process using one hand, while the other hand wraps around the proximal right upper limb, applying a gentle lateral pull to the left. This is performed 3–5 times. (2) To stretch the right lumbar muscles, including the quadratus lumborum and iliocostalis, the therapist stabilizes the right iliac crest with both hands while the patient actively bends the trunk to the left. The stretch is repeated 3–5 times. (3) The patient then bends the trunk actively to the right end range, holds the position for 8–10 s, and rests before repeating the motion 3–5 times. Once the movement is well controlled, balance disturbance exercises are introduced, such as applying light directional nudges or placing a balance cushion under the pelvis to stimulate proprioceptive response. (4) The therapist mobilizes the T1–T8 spinous processes using posterior-to-anterior techniques, repeated 8–10 times. Additionally, stretches are applied to the platysma, intercostal muscles, and upper rectus abdominis. Each stretch is held for 8–10 s and repeated 3–5 times. (5) Scapular mobilization is performed by stabilizing the axilla with one hand while the other hand mobilizes the inferior medial scapular edge in a medial-to-lateral and upward direction. Simultaneously, the pectoralis minor, subscapularis, and serratus anterior are stretched, each held for 8–10 s and repeated 3–5 times. (6) The humeral head is mobilized in multiple directions, superior, inferior, anterior, posterior, and rotational, within a pain-free range. Each direction is repeated 3–5 times. At the end of each movement, the patient is instructed to hold the final position, with assistance from the therapist if needed. (7) Finally, trigger points around the glenohumeral joint are compressed for 5–10 s, with pressure adjusted based on the patient’s tolerance. Refer to Figures 2–7 for specific procedural illustrations and schematic diagrams.

**Figure 2 fig2:**
[figure not shown]
Multidirectional humeral head mobilization therapy.

**Figure 3 fig3:**
[figure not shown]
Scapular repositioning.

**Figure 4 fig4:**
[figure not shown]
Subscapularis muscle release.

**Figure 5 fig5:**
[figure not shown]
Correction of thoracic kyphosis.

**Figure 6 fig6:**
[figure not shown]
Correction of thoracic kyphosis.

**Figure 7 fig7:**
[figure not shown]
Correction of thoracic transverse process deviation.

All treatments are delivered by certified DPS therapists to ensure both safety and accuracy. This structured approach effectively addresses biomechanical abnormalities, relieves post-stroke shoulder pain, and helps restore functional movement patterns.

### Standard Chinese Tuina regimen

SCTT is a widely practiced, non-pharmacological intervention recommended for managing shoulder pain, particularly periarthritis of the shoulder, as outlined in national teaching materials for Traditional Chinese Medicine education during China’s 13th Five-Year Plan (17). SCTT was selected as the control intervention in this study because it represents one of the most commonly applied and guideline-recognized manual therapies in China. In addition, our rehabilitation department is staffed with highly trained therapists who possess extensive clinical experience in tuina, ensuring consistent implementation and high treatment fidelity. These advantages make SCTT a representative and credible comparator for evaluating the clinical effectiveness of the DPS therapy.

In clinical practice, SCTT is typically performed with the patient in a seated position. The therapist begins by identifying painful or dysfunctional regions based on the patient’s reported symptoms and palpation findings. Core techniques such as pressing and kneading are applied to key acupoints, including Jianjing (GB21), Bingfeng (SI12), and Quchi (LI11), for approximately 2–3 min. This is followed by manipulations including kneading, rolling, grasping, and pinching, aimed at releasing muscle tension and stimulating soft tissues in commonly affected areas, particularly the supraspinatus, deltoid, and pectoralis minor muscles. After the initial muscle relaxation phase, treatment proceeds as follows:Muscle Relaxation and Release: The therapist stands on the affected side while the patient remains seated. One hand supports the patient’s upper arm in slight abduction, and the other applies rolling or kneading techniques over the anterior, deltoid, and posterior shoulder areas. Passive movements, abduction, external rotation, and internal rotation, are incorporated to ease spasms and help release adhesions.Spasm Relief and Pain Reduction: Point pressure and plucking techniques are applied to specific acupoints including Jianjing (GB21), Jianyu (LI15), Bingfeng (SI12), Tianzong (SI11), Jianzhen (SI9), Quchi (LI11), Shousanli (LI10), and Hegu (LI4). The therapist aims to produce a sensation of soreness and fullness. Plucking is used on tender or adhesive areas to relieve muscle spasms, reduce pain, and break down adhesions. Each point is stimulated for about 1 min.

The second phase of therapy emphasizes joint mobilization and improving circulation. The therapist begins by stabilizing the shoulder with one hand and using the other to hold the patient’s wrist or elbow, performing circular rotations of the shoulder joint, starting with smaller arcs and gradually increasing the range. Movements include adduction, abduction, extension, and internal rotation. Traction and stretching are applied to help free adhesions and increase joint range of motion. To improve circulation, grasping, rubbing, and pinching techniques are used around the shoulder region. The therapist then gently lifts and stretches the affected arm while applying traction and shaking. Finally, the shoulder, upper arm, and forearm are massaged using rubbing techniques, repeated 3–5 times, to stimulate blood flow and further relax the muscles. All procedures are carried out by licensed and experienced *tuina* therapists to ensure both safety and treatment effectiveness.

### Data analysis

Statistical analyzes will be performed using SPSS version 27.0. All continuous variables will be tested for normality using the Shapiro–Wilk test. Normally distributed data will be expressed as mean ± standard deviation and analyzed using independent sample *t*-tests for between-group comparisons and repeated measures ANOVA for within-group comparisons across time points (baseline, week 2, week 4, and 1-month follow-up). Non-normally distributed data will be reported as medians with interquartile ranges and assessed using the Mann–Whitney U test and Friedman test, respectively. Categorical variables such as gender or stroke type will be analyzed using chi-square tests or Fisher’s exact tests when appropriate. A two-sided *p*-value < 0.05 will be considered statistically significant for all analyzes.

For musculoskeletal ultrasound outcomes, four key indicators will be analyzed: (1) distance from the acromion to the greater tuberosity of the humerus and (2) thickness of the subdeltoid bursa will be treated as continuous variables and analyzed using the same approach as other quantitative measures—independent *t*-tests or Mann–Whitney U tests for between-group comparisons, and repeated measures ANOVA or Friedman tests for within-group changes. (3) Calcifications in the supraspinatus tendon and (4) effusion around the long head of the biceps tendon sheath will be treated as binary variables (presence/absence) and compared between groups using chi-square tests. All ultrasound images will be independently reviewed by two experienced sonographers blinded to group allocation. Inter-rater reliability will be evaluated using Cohen’s kappa for categorical variables and intraclass correlation coefficients (ICC) for continuous variables. Any discrepancies will be resolved by consensus discussion.

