**Figure 1 fig1:**
[figure not shown]
Study design flowchart: a detailed depiction of participant progression through each stage of the study.

The primary outcome is pain intensity, assessed using the VAS, a widely recognized and validated tool. VAS scores will be recorded at baseline, at 2 and 4 weeks during treatment, and again at a 1-month follow-up after completion of the intervention. Secondary outcomes assess shoulder joint function across four domains. First, ROM will be measured to evaluate mobility of the affected shoulder. Second, the absolute vertical distance difference between the medial superior angle of the scapula on the affected side and the second thoracic spinous process will be recorded. Third, musculoskeletal ultrasound will be used to assess five key indicators: presence of effusion around the long head of the biceps tendon sheath, calcification in the supraspinatus muscle, calcification at the insertion of the subscapularis tendon, subdeltoid bursa thickness (in millimeters), and the distance from the acromion to the greater tuberosity of the humerus. Lastly, the MBI will be used to evaluate overall independence in daily living activities. Covariates include age, sex, body mass index (BMI), stroke type (hemorrhagic or ischemic), and time since stroke onset. All outcome measures will be collected at baseline, 2 weeks, and 4 weeks after treatment begins. A follow-up VAS will be conducted 1 month post-intervention to assess the sustained effects of DPS in relieving post-stroke shoulder pain. The physical function assessments will be performed by trained evaluators blinded to treatment allocation, and data analysis will be conducted by statisticians also blinded to group assignments.

Detailed outcome variables and their classification as endpoints or intermediate measures are summarized in Table 1.

**Table 1 tab1:** Baseline assessment and sequence of trial measurements for primary and secondary outcomes.

	Before-intervention	Mid-intervention	Post-intervention	1-month follow-up
Time (weeks)	**0**	**2**	**4**	**8**
Baseline				
Sex (male/female)	**√**			
Type of stroke (ischemia/hemorrhage)	**√**			
Age, y	**√**			
BMI	**√**			
Time since stroke, y	**√**			
Primary outcome variable				
VAS	**√**	**√**	**√**	**√**
Secondary outcome variables				
Shoulder ROM				
Flexion (0–180°)	**√**	**√**	**√**	
Extension (0–50°)	**√**	**√**	**√**	
Abduction (0–180°)	**√**	**√**	**√**	
Adduction (0–40°)	**√**	**√**	**√**	

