### Sample size calculation

This study draws on findings from a previously published clinical observational trial on the application of DPS for post-stroke shoulder pain (15). Sample size estimation was performed using G*Power 3.1 software. The significance level (*α*) was set at 0.05, *β* at 0.20, and statistical power (1−β) at 0.80. Based on the method for comparing two groups of equal size and using an effect size (Cohen’s d = 0.91) as reported in the referenced study, the minimum required number of participants was calculated to be 19 per group, totaling 38. To account for an expected dropout rate of 20%, the sample size was increased to 48 participants. This adjustment ensures sufficient statistical reliability and helps maintain the study’s validity despite potential participant attrition.

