### Primary outcome

The primary outcome of this study is the change in VAS scores from baseline to 2 weeks, 4 weeks after the intervention, and at the 1-month follow-up. The VAS is a widely used and validated instrument for assessing subjective pain intensity. It consists of a 10 cm (100 mm) continuous line anchored by “no pain” at 0 and “worst imaginable pain” at 10 (18). Patients are instructed to mark the point on the line that best represents their current level of pain. The score is determined by measuring the distance in millimeters from the “no pain” anchor to the patient’s mark. The VAS is known for its sensitivity to changes in pain perception and is commonly used in clinical trials to evaluate the effectiveness of interventions. In this study, it functions as a key indicator of symptom change, providing a measurable outcome for assessing the degree of pain relief in patients with post-stroke shoulder pain (19).

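### A Shapiro–Wilk result on the trial data decides the test and effect measure for the primary VAS outcome, possibly differently at each visit, and neither route adjusts for baseline VAS

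*Protocol article*

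**What the plan says.** Data analysis sets a two-step rule. First, "All continuous variables will be tested for normality using the Shapiro–Wilk test". Then the result picks the route:

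- Pass: "Normally distributed data will be expressed as mean ± standard deviation and analyzed using independent sample *t*-tests for between-group comparisons", with repeated measures ANOVA within groups.
- Fail: "Non-normally distributed data will be reported as medians with interquartile ranges and assessed using the Mann–Whitney U test and Friedman test, respectively".

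The significance rule is the same on both routes: "A two-sided *p*-value < 0.05 will be considered statistically significant for all analyzes".

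The section on the primary outcome reads "The primary outcome of this study is the change in VAS scores from baseline to 2 weeks, 4 weeks after the intervention", and adds the 1-month follow-up. That makes three post-baseline comparisons. VAS is scored in millimetres on a 100 mm line, so it falls under the rule for continuous variables, and no exception is made for it.

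The Study design overview lists covariates: "Covariates include age, sex, body mass index (BMI), stroke type (hemorrhagic or ischemic), and time since stroke onset". Baseline VAS is not in that list, although Table 1 schedules it at week 0. Neither route in Data analysis uses a covariate.

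The Sample size calculation rests on a standardised mean difference: "using an effect size (Cohen’s d = 0.91) as reported in the referenced study".

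**The concern.** The two routes answer different questions. The t-test gives a difference in means. Mann–Whitney compares ranks, and the planned summary beside it is a median and interquartile range for each group. Which one becomes the primary result is known only after the outcome data have been tested.

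Two things are at stake.

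1. **Comparability across visits.** The rule covers every continuous variable and does not hold the VAS visits together. Week 2 could be reported as a mean difference and week 4 as a rank comparison. A reader could not then follow one treatment effect over time. On the rank route, the result is also no longer on the mean-based scale that was used to size the trial.
2. **Unused baseline information.** Baseline VAS is measured in every participant but enters neither planned between-group test as a covariate. In a trial of 48 that wastes precision. This is a separate matter from the normality rule, because it applies equally to both routes.

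**Working it through.** **1. The plan's own sample size.** Inputs from Sample size calculation: d = 0.91, α = 0.05, "and statistical power (1−β) at 0.80", 20% dropout. Data analysis makes the test two-sided.

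- n per group = 2 × (1.960 + 0.842)² / 0.91² = 18.96, so 19, or 38 in total.
- 38 / (1 − 0.20) = 47.5, so 48.

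Both stated figures reproduce by the normal approximation. The exact t calculation gives 20 per group (power 77.9% at 19, 80.1% at 20, 87.0% at 24). This difference does not affect the present point.

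**2. How often the visits end on different tests.** Assumptions, since the article does not state the unit of testing: Shapiro–Wilk at 0.05 in each arm at each visit, with Mann–Whitney used if either arm fails. Suppose the data are exactly normal and treat the visits as independent.

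- Chance of switching at one visit: p = 1 − 0.95² = 0.0975.
- Chance that the three visits do not share a test: 1 − p³ − (1 − p)³ = 1 − 0.0009 − 0.7351 = 0.264.

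So about 26% of trials are mixed with no departure from normality at all. Simulations agree: 25.6% with normal data and between-visit correlation 0.6, and about 25–28% for VAS change scores with correlation 0.5. With skewed data (lognormal, again an assumption) the figure was 67% for sigma 0.3 and 51% for sigma 0.5.

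**3. Does the choice matter for the conclusion?** With 19 per arm, the two tests gave different significance verdicts at one visit in 2–3% of runs under no effect, and in 7–11% at d = 0.91. Type I error of the two-step rule at one visit was 4.7–5.8%, with simulation error of about 0.5 points.

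**4. Does the pre-test cost power?** One simulation (19 per arm; correlation 0.5; baseline mean 6 limited to 4–10; control follow-up mean 3.0, SD 1.65, floor at 0; all assumed) separates the two issues:

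| Analysis | 1.2 cm effect | 1.5 cm effect |
|---|---|---|
| Follow-up score, pre-tested | 59.0% | 77.2% |
| Follow-up score, fixed t-test | 59.2% | 77.6% |
| Change score, pre-tested | 62.2% | 78.7% |
| Change score, fixed t-test | 62.2% | 78.8% |
| ANCOVA on baseline VAS | 68.9% | 86.7% |

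Removing the pre-test gains 0.4 points at most. The gap is to ANCOVA.

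**5. Size of the gain from adjustment.** As an illustration, treat the plan's d = 0.91 as applying to follow-up scores (the article does not say which scale it is on), with correlation ρ = 0.5 and 19 per arm. Power ≈ Φ(d × √(19/2) − 1.96).

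- Follow-up score: 0.91 × 3.082 = 2.805, so Φ(0.845) = 80.1%.
- ANCOVA: residual variance factor 1 − ρ² = 0.75, d = 0.91/√0.75 = 1.051, so Φ(1.279) = 90.0%. The gain is about 10 points.
- Change score: variance factor 1 + k² − 2ρk, where k is the baseline SD divided by the follow-up SD.
  - k = 0.75: factor 0.8125, d = 1.010, power 87.5%, so ANCOVA gains 2.5 points.
  - k = 0.80: factor 0.84, d = 0.993, power 86.4%, gain 3.5 points.
  - k = 1: factor 1, power 80.1%, gain about 10 points.
  - k = 0.5: factor 0.75, the same as ANCOVA, no gain.

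The entry threshold of VAS ≥ 4 narrows the baseline spread, so k below 1 is plausible. Two further simulations at 1.2 and 1.5 cm are in line with this. One gave ANCOVA 72% and 88%, against 60% and 80% on follow-up scores and 68% and 86% on change scores. The other gave 63% against 60%, and 79% against 76%, on change scores. The simulation in step 4 gave a larger gap to change scores, 6.7 and 8.0 points.

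**The case against.** The best defence is that the rule is written down beforehand, names both tests, and is statistically valid, since type I error stays near nominal. The article also does not say that normality is tested per arm and per visit. Testing once per variable would put all three visits on one test, and such detail is often left to an analysis plan. That much stands, so the 25–28% is conditional on the assumed unit of testing. It does not remove the point. Even under a single test per variable, the data would still choose the primary effect measure. Moreover, the article states the data-driven rule outright, so a plan that fixed one test would have to override it.

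Three stronger readings are tempting and are not supported:

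- **That the normality rule lowers power.** A fixed t-test and the pre-tested rule perform alike. The loss comes from not adjusting for baseline.
- **That the choice of test depends on the treatment effect, because VAS has a floor at 0.** On raw follow-up scores the rank route was chosen in 9%, 28% and 44% of runs at effects of 0, 1.2 and 1.5 cm. On change scores, which the section on the primary outcome names, it was chosen in 10%, 10% and 11%, close to the 9.75% expected by chance.
- **That lack of adjustment is peculiar to the non-parametric route.** The independent t-test is equally unadjusted, and change scores take baseline into account by subtraction on both routes.

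**Conclusion.** The point holds as two linked but separate weaknesses. First, the primary effect measure is left to a preliminary test on the trial data and may differ between visits. The chance is about 25–28% on change scores if normality is tested per arm and visit at 0.05, and higher if the scores are skewed. Second, neither planned route adjusts for baseline VAS. With correlation 0.5 and 19 per arm this costs roughly 10 points of power against follow-up scores. Against change scores it costs about 2–4 points when the baseline SD is about three quarters to four fifths of the follow-up SD, and anything from none to about 10 points as that ratio runs from 0.5 to 1. The correlation, the SDs and the unit of testing are assumptions, because the article gives none of them.

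This is a matter of clarity and efficiency. The planned tests are not invalid, and the sample size is not called into question by it. The change is worth making because it is free.

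**What to change.** In Data analysis:

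1. Remove the Shapiro–Wilk rule as the selector of the test for VAS and the other continuous outcomes. Check model residuals instead, without letting the check change the primary analysis.
2. Name one analysis for VAS at week 2, week 4 and the 1-month follow-up: ANCOVA at each visit, or a mixed model for repeated measures, with baseline VAS as covariate. State which of the covariates listed in the Study design overview also enter.
3. Report the adjusted mean difference with its 95% CI at every visit.
4. Keep the rank-based comparison, or a bootstrap or permutation version of the adjusted analysis, as a sensitivity analysis specified in advance.
5. Treat the other continuous outcomes in the same way, each with its own baseline value.

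The cost is wording only. Baseline VAS is already scheduled, no visit or measurement is added, and the planned 48 participants can stay. The change should be made before outcome data are seen by group.

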### Randomization

Once written informed consent was obtained and baseline assessments were completed, an off-site research assistant performed the randomization using SPSS version 27. Participants were randomly assigned to either the DPS therapy group or the SCTT group. To reduce potential allocation bias, stratified randomization was applied based on time since stroke (in years) and stroke type (ischemic or hemorrhagic).

To ensure allocation concealment, all information regarding group assignment, therapy schedules, and intervention locations was communicated solely through centralized telephone contact, managed by the off-site research assistant. This method kept other study personnel blinded to group assignments and helped minimize bias throughout the intervention phase.

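### The stated between-arm test adjusts for neither baseline VAS nor the two stratification factors: valid, but avoidably imprecise with about 38 completers

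*Protocol article*

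**What the plan says.** The Data analysis section assigns continuous outcomes to tests as follows: "Normally distributed data will be expressed as mean ± standard deviation and analyzed using independent sample" t-tests between groups, with repeated measures ANOVA reserved for changes within each group. For non-normal data, the Mann–Whitney U and Friedman tests take these two roles. The section contains no regression, ANCOVA, mixed model or stratified test.

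Two other sections bear on this. Under Randomization, "stratified randomization was applied based on time since stroke (in years) and stroke type (ischemic or hemorrhagic"). In the Study design overview, after Figure 1: "Covariates include age, sex, body mass index (BMI), stroke type (hemorrhagic or ischemic), and time since stroke onset". The last two of these covariates are the stratification factors. Table 1 shows all five, and VAS, recorded at baseline. No stated analysis uses the list of covariates.

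The outcome that enters the test is described in two ways. The abstract and the Primary outcome section call it change in VAS from baseline. The Study design overview and the opening of Assessment of outcomes call it pain intensity on the VAS. The Data analysis section does not say which one is tested.

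**The concern.** The protocol names covariates and stratifies on two of them, then commits by name to tests that cannot use any of them. Because the tests are named, this is not a detail left open for an unseen analysis plan.

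What is at stake is precision on the primary outcome. Patients must enter with a VAS of at least 4, and their later pain is likely to be related to where they started. With about 19 completers per arm, chance differences in baseline VAS are plausible. A test on visit scores does not correct for them. A test on change scores subtracts the full baseline value, which over-corrects whenever the regression slope of follow-up on baseline is below 1. Stratifying and then leaving the strata out of the analysis can also give away some of what the stratification was meant to buy.

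**Working it through.** **Inputs from the protocol.** Sample size calculation gives a target power of 0.80, an effect size of d = 0.91 taken from an earlier study, a resulting 19 per arm (38 in all), and an increase to 48 for an assumed 20% loss. Data analysis sets the significance level at 0.05, two-sided. Allocation is 1:1 (Enrollment and the informed consent process).

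**Assumptions.** The protocol gives no correlation r between baseline and follow-up VAS, so r = 0.3, 0.5 and 0.7 are shown. On the effect size it says only this: "using an effect size (Cohen’s d = 0.91) as reported in the referenced study". Whether d = 0.91 is scaled by the SD of the post-treatment score or of the change score is not stated, so both are shown. The variance formulas assume equal variances at baseline and follow-up.

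**Step 1: the plan's own figure.** n per arm = 2 × ((1.960 + 0.842) / 0.91)² = 18.96, so 19 per arm and 38 in all. 38 / (1 − 0.20) = 47.5, so 48. The figure reproduces, and it rests on an unadjusted two-group comparison. At 19 per arm its power is 0.80 by the normal approximation and 0.78 by the noncentral t distribution. The noncentral t is used below.

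**Step 2: variance of the three candidate analyses**, relative to a t-test on visit scores (= 1):
- t-test on change: 2(1 − r)
- ANCOVA on baseline VAS: 1 − r²
- ANCOVA relative to change: (1 − r²) / (2(1 − r)) = (1 + r) / 2

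| r | ANCOVA / visit score | Reduction | ANCOVA / change | Reduction |
|---|---|---|---|---|
| 0.3 | 0.91 | 9% | 0.65 | 35% |
| 0.5 | 0.75 | 25% | 0.75 | 25% |
| 0.7 | 0.51 | 49% | 0.85 | 15% |

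**Step 3: power at 19 completers per arm, d = 0.91.** The effect size becomes d / √(variance ratio). ANCOVA has 35 degrees of freedom and the t-tests have 36.

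| r | d on post-score SD: visit-score t | change t | ANCOVA | d on change SD: change t | ANCOVA |
|---|---|---|---|---|---|
| 0.3 | 0.78 | 0.64 | 0.82 | 0.78 | 0.92 |
| 0.5 | 0.78 | 0.78 | 0.88 | 0.78 | 0.88 |
| 0.7 | 0.78 | 0.94 | 0.97 | 0.78 | 0.84 |

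**Step 4: allowing for the cost of adjustment.** Step 3 charges one degree of freedom but nothing for chance imbalance in the covariates. For k covariates and N = 38, an approximate inflation factor is 1 + k / (N − k − 3). With baseline VAS alone this is 1 + 1/34 = 1.03. With baseline VAS and both stratification factors it is 1 + 3/32 = 1.09. The unfavourable case is that the two factors explain nothing and are balanced only by chance. ANCOVA with all three terms (33 degrees of freedom) then has power 0.78 / 0.85 / 0.95 with d on the post-score SD and 0.90 / 0.85 / 0.81 with d on the change SD, at r = 0.3 / 0.5 / 0.7. At worst it breaks even with 0.78.

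**Step 5: the stratification factors.** Suppose the strata explain a share R² of the outcome variance and the randomisation balances them. The unadjusted standard error is then too large by 1/√(1 − R²), and the nominal 5% test runs at about 0.045, 0.039, 0.030 and 0.021 for R² = 5%, 10%, 20% and 30%.

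**Step 6: the whole covariate list.** Entering all five named covariates, without baseline VAS, gives power of about 0.71 if they explain nothing, 0.76 at R² = 0.10 and 0.80 at R² = 0.20, against 0.78 unadjusted.

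**The case against.** An unadjusted comparison of randomised arms is valid, matches the basis of the sample size, and is not shown to be underpowered at the trial's own effect size beyond the difference between 0.78 and 0.80. No bias or inflated type I error arises. That stands, and it makes this a matter of efficiency.

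Four stronger readings are tempting, and the protocol does not support them:

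- **That the test ignores baseline VAS.** The abstract and the Primary outcome section define the outcome as change, which uses baseline by subtraction. What is missing is adjustment for baseline as a covariate.
- **That power is really about 64%.** This needs a low correlation, d scaled by the post-score SD, and a test on change, all at once. The protocol does not state which SD d refers to. If it is the change SD, the change-score test has power 0.78 at every r.
- **That stratification makes the unadjusted standard error too large.** This needs strata that are both prognostic and balanced by the randomisation. The Randomization section names no blocking or minimisation, so balance within strata is not established. Where both conditions hold, the error is in the conservative direction.
- **That leaving out every named covariate loses precision.** Step 6 shows that the full list can cost power if its members are weakly prognostic. The case rests on baseline VAS and, conditionally, on the two stratification factors, not on age, sex and BMI.

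It can also be said that an article leaves covariate handling to the analysis plan. That would cover a supporting analysis. It does not cover the main between-arm test, which the article names.

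**Conclusion.** The point holds as one of avoidable imprecision. The stated between-arm test does not adjust for baseline VAS as a covariate and omits both stratification factors, although all three are collected at baseline. Adjusting for baseline VAS lowers the variance on either reading of the outcome. Over r = 0.3 to 0.7 it raises power at 19 per arm and d = 0.91 from 0.78 to 0.82–0.97 (d on the post-score SD) or 0.84–0.92 (d on the change SD).

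The size depends on r and on the scaling of d, neither of which the protocol gives, so the gain cannot be fixed to one number. At its smallest, against visit scores at r = 0.3, it is a few points and can be used up by uninformative stratum terms. It matters more if the true effect is below the planned one: at d = 0.6 and r = 0.5, power is 0.44 unadjusted and 0.55 with ANCOVA. The result of the trial would not be invalid without the change.

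**What to change.** State in Data analysis that the primary between-group comparison is an ANCOVA of VAS on arm, baseline VAS, stroke type and time since stroke, or the corresponding contrast of a mixed model over the visits. Analyse each continuous secondary outcome in the same way with its own baseline value. Keep the unadjusted t-test or Mann–Whitney U test as a sensitivity analysis. Use age, sex and BMI only in a pre-specified sensitivity analysis, and say so where the covariates are listed.

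With baseline VAS as a covariate, the choice between change and visit score no longer alters the estimated arm difference, because both give the same treatment coefficient.

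The cost is wording and about three degrees of freedom, with time since stroke entered as a single term. No new data are needed and the sample size can stay at 48.
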